### Quality assurance

This protocol has been reviewed and revised several times by experts on acupuncture, neurology, statistics, and methodology. Before the trial, all researchers will be required to attend a series of training sessions, which will ensure that the personnel involved fully understand the trial protocol and standard operating procedures of the study. The Data Monitoring Committee (DMC) will comprise the PI, the CRC, and a researcher who are not involved in the data collection portion of the clinical trial. The DMC, which is independent from the sponsor and competing interests, will manage the data to ensure its validity. In the event that the protocol described herein is revised, the revisions will require approval from the IRB of DongShin University Gwangju Korean Medicine Hospital.

### Sample size estimation

We had no preliminary study or adequate previous studies upon which to base our estimate of sample size. Considering funding, the single-center study design, and time constraints, the maximum possible number of participants was set at 32; therefore, we adopted a pilot study design with eight participants in each of four groups.

As our study is a pilot study, the sample size will not be sufficient for determining the efficacy of acupuncture on MCI. Our study will indicate whether it is feasible to randomize participants to a trial of acupuncture treatment for MCI and suggest whether acupuncture is an acceptable treatment for the included participants.

### Statistical analysis

A statistician, who is not involved in data collection, will analyze the final data. We will perform a full analysis (FA) set to assess efficacy and a supplementary per-protocol (PP) analysis. We will compare the results of statistical analyses between the PP group and the FA group, and confirm whether there is a statistically significant difference between groups. If there is a significant difference between the PP and FA groups, the cause will be reviewed and reflected in the efficacy assessment. All statistical analyses will be performed using SPSS version 21 software.

Baseline characteristics will be described and compared among the groups. Continuous data will be presented as the mean and standard deviation, and compared using the independent *t* test or Wilcoxon rank-sum test. Categorical data will be presented as the frequency and percentage, and compared using the chi-square or Fisher’s exact test.

Within each group, changes in ADAS-K-cog, MoCA-K, CES-D, K-ADL, K-IADL, and EQ-5D-5L scores at 8 weeks (i.e., the end of the intervention) and 20 weeks (i.e., 12 weeks after the end of the intervention) after the start of the intervention will be analyzed relative to baseline scores using paired *t* tests or Wilcoxon signed-rank tests. The degree of change at each time point will be evaluated by repeated-measures analysis of variance and two-sample *t* tests or Wilcoxon rank-sum tests. Subanalyses will be performed according to participant age. All reported *P* values will be two-tailed with 95% confidence intervals. *P* < 0.05 will be considered statistically significant.

Missing values will be obtained using the last observation carried forward method. Interim analyses will not be performed.

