## Methods/design

### Aims

We intend to obtain basic data for developing an optimal acupuncture treatment for MCI by comparing the effects of different acupuncture treatment methods (variable acupoint specificity, needle duration, and electrical stimulation) on cognitive function in MCI patients. Our study will indicate whether it is feasible to randomize participants to different acupuncture treatments for MCI and suggest whether acupuncture is an acceptable treatment for the included participants. The results of this study will be the basis of a future clinical trial to investigate the effects of optimal acupuncture treatment for MCI.

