### Hypothesis

The null hypothesis is that randomization of patients into four equal groups each receiving a different acupuncture protocol is not feasible and/or acupuncture is not safe for MCI patients and different acupuncture treatment methods will provide similar improvements in cognitive function in MCI patients.

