### Study design and setting

This study is a prospective, outcome-assessor-blinded, parallel-arm, single-center (DongShin University Gwangju Korean Medicine Hospital, Republic of Korea), randomized controlled clinical trial with a 1:1:1:1 allocation ratio. A total of 32 participants, who meet the inclusion and exclusion criteria, will be randomly allocated to a basic acupuncture (BA), an acupoint specificity (AS), a needle duration (ND), or an electroacupuncture (EA) group (*n* = 8 each). The patients will receive acupuncture treatment once per day, 3 days/week for 8 weeks.

The outcome measure will be improvement in cognitive function evaluated using the Korean version of the Alzheimer’s Disease Assessment Scale—cognitive subscale (ADAS-K-cog) and the Korean version of the Montreal Cognitive Assessment (MoCA-K), and improvement in scores on the Center for Epidemiological Studies Depression (CES-D), Korean Activities of Daily Living (K-ADL), Korean Instrumental Activities of Daily Living (K-IADL), and European Quality of Life Five Dimension Five Level (EQ-5D-5L) scales. All scores will be recorded at baseline (before intervention), 8 weeks after the first intervention (i.e., at the end of the intervention period), and 12 weeks after completion of the intervention.

The design of this study, including outcomes measured and evaluation schedules, is based on the designs of several previous studies that have evaluated acupuncture treatment for cognitive impairment [11, 12, 15]. This manuscript has been written in accordance with the Standard Protocol Items: Recommendations for Interventional Trials (SPIRIT) and Consolidated Standards Of Reporting Trials (CONSORT) 2010 guidelines [16, 17] (see Additional file 1).

This study protocol complies with the principles of the Declaration of Helsinki and Korean Good Clinical Practice guidelines. The trial has been registered at http://cris.nih.go.kr (registration number: KCT 0003430; registration date: 16 January 2019). The study design is summarized in Figs. 1 and 2.

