### Inclusion criteria

Participants meeting all of the following criteria will be included in this trial: male or female aged 55–85 years; fulfillment of the Petersen diagnostic criteria for MCI [1] (i.e., subjective memory complaint, normal general cognitive function, objective memory impairment, not severe enough to interfere with ADL, and no dementia) with memory impairment for at least the 3 months preceding enrollment; score of 20–23 on the Korean version of the Mini-Mental State Examination (MMSE); score of 0–22 on the MoCA-K; sufficient language fluency to reliably complete all study assessments; and willingness to sign the informed consent form.

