4. Other treatment components	4a) Details of other interventions administered to the acupuncture group	None
	4b) Setting and context of treatment—including instructions to practitioners—as well as information and explanations given to patients	Practitioner–patient conversation about the context of the treatment, life habits, and daily life management
5. Practitioner background	5a) Description of participating acupuncturists	Korean medicine doctor with the following qualifications: 6 years of formal university training in Korean medicine and a license
6. Control or comparator interventions	6a) Rationale for the control or comparator in the context of the research question, with sources that justify the choice	[9]
	6b) Precise description of the control or comparator; details for items 1–3 with the use of sham acupuncture or any other type of acupuncture-like control	This study will investigate the optimal acupuncture treatment method for the treatment of mild cognitive impairment (MCI) through a comparison of the effects of different acupuncture treatment methods according to acupoint specificity, needle duration, and electrical stimulation in terms of an improvement in cognitive function in patients with MCI. There is no control or comparator

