Needle duration refers to the duration for which the needle is held at an acupoint after needle manipulation, with the aim of awaiting Qi arrival, regulating Qi circulation, eliminating pathogenic factors, and reinforcing antipathogenic Qi as well as the effect of manipulation. Different diseases require different durations of needle retention for treatment [14]. In the ND group in this study, we will adopt a 20-min needle duration, as described in a previous acupuncture study on cognitive impairment [22]. There are some methods of reinforcing or reducing acupuncture manipulations in TCM, which involve slow and quick needle manipulation and needle manipulation in concordance with the patient’s respiration. All manipulations are based on the principle of puncturing along and against the directional flow of the meridian Qi. Since stimulation gained by needle manipulation cannot be quantified, the EA group in this study will receive electrical stimulation, which was used in a previous acupuncture study on MCI [9].

In our study, cognitive function will be assessed using the K-MMSE and MoCA-K scales in the initial screening session. The MMSE is one of the more commonly used evaluation tools for cognitive function and the MoCA scale is a simple and highly sensitive cognition screening tool. Using the MMSE and MoCA scales for identifying possible cases of MCI is a first-step screening strategy for MCI [36]. We will use the ADAS-K-cog, MoCA-K, CES-D, K-ADL, K-IADL, and EQ-5D-5L scales for investigating the effects of different acupuncture treatment methods on cognitive function, depression, ADL, and quality of life in patients with MCI.

This protocol has some limitations. First, because of the lack of adequate preliminary studies and limited funding, this survey has been designed as a single-center pilot study with a small sample size. Second, while previous acupuncture studies on cognitive impairment have used body and scalp acupoints [22, 25, 26, 37], we will only use scalp acupoints for basic acupuncture treatment. Third, although all outcomes will be measured and recorded by an independent researcher in order to minimize the risk of detection bias, we cannot adopt a double-blind procedure because of the nature of acupuncture treatment.

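### The planned within-arm paired tests cannot show benefit because no arm is untreated; the between-arm tests are valid but are not adjusted for the baseline score as a covariate

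*Protocol article*

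**What the plan says.** All places are in the protocol article.

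- **Within-arm tests.** Under Statistical analysis, each arm's scores on six scales at 8 and 20 weeks "after the start of the intervention will be analyzed relative to baseline scores using paired" t tests or Wilcoxon signed-rank tests. Significance is set at two-sided P < 0.05. The same section assigns the full analysis set to the assessment of efficacy.
- **Between-arm tests.** The next sentence reads "The degree of change at each time point will be evaluated by repeated-measures analysis of variance and two-sample" t tests or rank-sum tests. No baseline covariate is named.
- **Comparator.** Under Interventions, Table 1 item 6b states "There is no control or comparator". All four arms of eight receive active acupuncture.
- **Question.** The Aims describe "comparing the effects of different acupuncture treatment methods (variable acupoint specificity, needle duration, and electrical stimulation) on cognitive function in MCI patients". The effect part of the null hypothesis is that "different acupuncture treatment methods will provide similar improvements in cognitive function in MCI patients".
- **MoCA-K.** It is an outcome and also an entry criterion: "score of 0–22 on the MoCA-K". The Discussion says that "cognitive function will be assessed using the K-MMSE and MoCA-K scales in the initial screening session".

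**The concern.** A paired test in a single arm asks whether the mean score moved. It does not ask why. With no untreated, sham or waiting-list arm, movement can come from acupuncture, from taking the same cognitive tests three times, from natural course or, on a scale used to select participants, from regression to the mean. The test cannot tell these apart.

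The tests also do not answer the trial's question. Aims and Hypothesis concern differences between methods, and a pattern of significance in some arms and not in others is not a test of a difference. With eight per arm, such patterns arise easily when all arms change equally. The results are meant to be the basis of a later trial of an optimal method, so an arm favoured in this way could be carried forward.

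A smaller issue concerns efficiency. The between-arm comparison does not use the baseline score as a covariate, although every participant's baseline is collected.

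**Working it through.** The document gives no SD, correlation, effect size or power. The sample of 32 was set by funding, the single centre and time, so there is no statistical figure to reproduce; 4 x 8 = 32 is consistent. Shifts, correlations, reliabilities and the MoCA-K distribution below are assumptions, shown as ranges.

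**1. Number of within-arm tests.** 4 arms x 6 scales x 2 times = 48.

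**2. Within-arm significance with no specific effect.** Let d be a non-specific shift shared by all arms, in SDs of the change score. For n = 8, the paired t statistic has 7 degrees of freedom and noncentrality d x sqrt(8). Let p be the two-sided rejection probability at 0.05. For one scale at one time:
- at least one of four arms significant: 1 - (1 - p)^4
- arms disagree (some significant, some not): 1 - (1 - p)^4 - p^4

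| d | p per arm | at least one of four | arms disagree |
|---|---|---|---|
| 0 | 0.05 | 0.185 | 0.185 |
| 0.25 | 0.094 | 0.327 | 0.326 |
| 0.5 | 0.232 | 0.652 | 0.649 |
| 0.75 | 0.449 | 0.908 | 0.867 |
| 1.0 | 0.681 | 0.990 | 0.775 |

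At d = 0.5: 1 - 0.768^4 = 1 - 0.348 = 0.652, and 0.652 - 0.232^4 = 0.652 - 0.003 = 0.649. So about two times in three the arms would disagree although all four have the same true change. Simulation (20,000 runs) gave 0.232 to 0.233 per arm.

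**3. MoCA-K.** If the screening score is the baseline, the expected rise on retest is (1 - reliability) x SD x phi(a)/Phi(a), with a = (22.5 - mean)/SD. For a screened-population mean of 22 to 24, SD 3 to 4 and reliability 0.7 to 0.9, the rise is about 0.2 points (mean 22, SD 3, reliability 0.9) to 1.3 points (mean 24, SD 4, reliability 0.7). If MoCA-K is measured again after screening and that score is the baseline, this component disappears under the same model. A practice effect can remain.

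**4. Between-arm tests of change.** With the same 0.5 SD shift in both arms, simulated error rates were 0.049 to 0.051 at correlations of 0.5 to 0.8, with no bias. Shared shifts cancel.

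**5. Gain from baseline adjustment.** In units of the raw score variance, the change score has variance 2(1 - r) and ANCOVA has 1 - r^2, where r is the baseline-to-follow-up correlation. The large-sample ratio is 2/(1 + r). Estimating the slope costs a factor 1 + 1/26 in a four-arm model (28 within-arm degrees of freedom) and 1 + 1/12 in an 8 v 8 analysis.

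| r | ratio, large sample | ratio, four-arm | variance cut, four-arm | ratio, 8 v 8 |
|---|---|---|---|---|
| 0.5 | 1.33 | 1.28 | 22% | 1.23 |
| 0.7 | 1.18 | 1.13 | 12% | 1.09 |
| 0.8 | 1.11 | 1.07 | 7% | 1.03 |
| 0.9 | 1.05 | 1.01 | 1% | 0.97 |

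Example at r = 0.7: (2/1.7) x (26/27) = 1.133, and 1 - 1/1.133 = 0.12. In separate 8 v 8 analyses at r = 0.9, adjustment is slightly worse than change scores.

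**The case against.** **The study is a pilot and says so.** Sample size estimation states that the sample cannot determine efficacy, and the Discussion expects only preliminary evidence. No sentence says that a within-arm P value will be taken as proof of benefit. This tempers the concern but does not remove it. The disclaimer is about numbers, whereas the missing comparator would matter at any sample size. Statistical analysis still speaks of assessing efficacy and puts no limit on how the 48 P values may be read.

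**The between-arm tests are sound.** A reader might infer that they ignore baseline, or that practice effects and regression to the mean bias them. The document does not support either reading. The tests are applied to the degree of change, so baseline is subtracted, and shifts shared by randomized arms cancel. Comparing change scores is valid, and a covariate is an efficiency choice that a fuller analysis plan may yet add. This stands, and it limits the second part of the point to precision.

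**The MoCA-K argument is narrow.** It touches one of six scales, hence 8 of the 48 tests. It also depends on the screening score being the baseline. The Discussion mentions an initial screening session, while Randomization mentions completing baseline measurements; the article does not say whether these give the same score. This too stands, so the regression figure is conditional.

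**The probabilities count significance in either direction.** At zero shift, half of the 18.5% would be worsening. At a shift of 0.5 SD nearly all significant results are in the direction of the shift.

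**Conclusion.** The point holds for the within-arm tests. They are a stated analysis, they cannot attribute change to acupuncture because every arm is treated, and they do not compare methods. At an assumed non-specific shift of 0.5 SD of change, 23% of arms of eight would be significant and at least one of four would be so 65% of the time. Over shifts of 0.25 to 1.0 SD the latter figure runs from 33% to 99%. The size depends on the assumed shift; the logical defect does not. For MoCA-K, regression to the mean of about 0.2 to 1.3 points is added only if the screening score is the baseline.

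The between-arm tests are unbiased as planned. Baseline adjustment in a four-arm model would be a modest gain in precision, 7% to 22% of variance at correlations of 0.8 to 0.5 and close to nil at 0.9. It is an improvement, not the correction of an error.

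**What to change.** 1. Under Statistical analysis, replace the within-arm paired tests by mean change with 95% confidence interval for each arm, scale and time, without P values. Label these as descriptive and say that change from baseline will not be attributed to acupuncture. The label is needed because a confidence interval that excludes zero is otherwise the same paired t test.
2. Base inference on the contrasts of AS, ND and EA with BA, since each of these arms is defined as BA with one feature changed. Take them from a single four-arm ANCOVA, or a mixed model covering weeks 8 and 20, with the outcome's own baseline score as covariate.
3. State which MoCA-K score is the baseline. Where MoCA-K is measured again after the qualifying screening test, use the later score.

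The cost is a change of wording. The data are already collected. The covariate takes one degree of freedom (28 to 27 in the four-arm model), with little or no gain if the correlation is near 0.9.

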### Confidentiality and data management

All identification records of the participants will be kept confidential. When the results of the study are published, the identification records will be accessed with IRB approval and the participants’ names will appear as initials to protect individuals’ identities, if necessary. All documents related to the trial, including case report forms (CRFs), will be recorded and labeled with participant identification codes and will not reveal the names of participants. The serial number codes will be stored in sealed, opaque envelopes and kept in a double-locked cabinet. All participant data will be recorded in Excel files by the CRC. All data will be checked by the CRC and rechecked by a researcher, both of whom are not included in this study’s data collection phase to ensure the reliability of the data. Continuous data will be coded as data values and categorical data will be coded as number sets for each item by a statistician who is not involved in the data collection phase of this clinical trial. The entry and coding of data will be double-checked. Electronic data will be stored on a password-protected computer. Anyone who is not approved by the IRB will not be able to access the data. In addition, raw data (i.e., CRFs) will be stored in a cabinet until the end of the study. Written informed consent for the publication of individuals’ details and accompanying images will be obtained from the participants.

## Discussion

Apart from needle insertion, factors such as needle sensation, psychological factors, acupoint specificity, needle duration, and acupuncture manipulation also influence the therapeutic effects of acupuncture [14]. Among these factors, acupoint specificity, needle duration, and acupuncture manipulation are objective. It is, therefore, necessary to identify the optimal acupoint specificity, needle duration, and acupuncture manipulation techniques in order to develop an optimal acupuncture treatment method for MCI. Although acupuncture has long been used to treat cognitive dysfunction, the optimal acupuncture treatment method for cognitive impairment has been understudied and is yet to be established. This study is expected to provide preliminary evidence for how to develop the optimal acupuncture treatment method for MCI.

For the acupoints and needle duration of the BA group, we adopted the acupuncture treatment procedures most commonly used in previous clinical trials on cognitive impairment and dementia [11, 12, 15]. According to the theory of traditional Chinese medicine (TCM), acupoint specificity is an important basis for clarifying the functionality of acupoints. The choice and compatibility of acupoints are considered to have a direct impact on the therapeutic effect [14]. The AS group in this study will receive acupuncture at KI3 in addition to the same treatment administered to the BA group. KI3 is one of the more frequently used acupoints and is reported to have a varying efficacy in the treatment of dementia [35]. Previous functional magnetic resonance imaging studies have indicated that acupuncture at KI3 can activate certain cognition-related regions [18–21].

Needle duration refers to the duration for which the needle is held at an acupoint after needle manipulation, with the aim of awaiting Qi arrival, regulating Qi circulation, eliminating pathogenic factors, and reinforcing antipathogenic Qi as well as the effect of manipulation. Different diseases require different durations of needle retention for treatment [14]. In the ND group in this study, we will adopt a 20-min needle duration, as described in a previous acupuncture study on cognitive impairment [22]. There are some methods of reinforcing or reducing acupuncture manipulations in TCM, which involve slow and quick needle manipulation and needle manipulation in concordance with the patient’s respiration. All manipulations are based on the principle of puncturing along and against the directional flow of the meridian Qi. Since stimulation gained by needle manipulation cannot be quantified, the EA group in this study will receive electrical stimulation, which was used in a previous acupuncture study on MCI [9].

In our study, cognitive function will be assessed using the K-MMSE and MoCA-K scales in the initial screening session. The MMSE is one of the more commonly used evaluation tools for cognitive function and the MoCA scale is a simple and highly sensitive cognition screening tool. Using the MMSE and MoCA scales for identifying possible cases of MCI is a first-step screening strategy for MCI [36]. We will use the ADAS-K-cog, MoCA-K, CES-D, K-ADL, K-IADL, and EQ-5D-5L scales for investigating the effects of different acupuncture treatment methods on cognitive function, depression, ADL, and quality of life in patients with MCI.

This protocol has some limitations. First, because of the lack of adequate preliminary studies and limited funding, this survey has been designed as a single-center pilot study with a small sample size. Second, while previous acupuncture studies on cognitive impairment have used body and scalp acupoints [22, 25, 26, 37], we will only use scalp acupoints for basic acupuncture treatment. Third, although all outcomes will be measured and recorded by an independent researcher in order to minimize the risk of detection bias, we cannot adopt a double-blind procedure because of the nature of acupuncture treatment.

